## Abstract

**Background:**

Chronic localized pain syndromes, especially chronic low back pain (CLBP), are common reasons for consultation in general practice. In some cases chronic localized pain syndromes can appear in combination with chronic widespread pain (CWP). Numerous studies have shown a strong association between CWP and several physical and psychological factors. These studies are population-based cross-sectional and do not allow for assessing chronology. There are very few prospective studies that explore the predictors for the onset of CWP, where the main focus is identifying risk factors for the CWP incidence. Until now there have been no studies focusing on preventive factors keeping patients from developing CWP.

Our aim is to perform a cross sectional study on the epidemiology of CLBP and CWP in general practice and to look for distinctive features regarding resources like resilience, self-efficacy and coping strategies. A subsequent cohort study is designed to identify the risk and protective factors of pain generalization (development of CWP) in primary care for CLBP patients.

**Methods/Design:**

Fifty-nine general practitioners recruit consecutively, during a 5 month period, all patients who are consulting their family doctor because of chronic low back pain (where the pain is lasted for 3 months). Patients are asked to fill out a questionnaire on pain anamnesis, pain-perception, co-morbidities, therapy course, medication, socio demographic data and psychosomatic symptoms. We assess resilience, coping resources, stress management and self-efficacy as potential protective factors for pain generalization. Furthermore, we raise risk factors for pain generalization like anxiety, depression, trauma and critical life events. During a twelve months follow up period a cohort of CLBP patients without CWP will be screened on a regular basis (3 monthly) for pain generalization (outcome: incident CWP).

**Discussion:**

This cohort study will be the largest study which prospectively analyzes predictors for transition from CLBP to CWP in primary care setting. In contrast to the typically researched risk factors, which increase the probability of pain generalization, this study also focus intensively on protective factors, which decrease the probability of pain generalization.

**Trial registration:**

German Clinical Trial Register DRKS00003123

## Background

Chronic localized pain syndromes, especially chronic low back pain (CLBP), are common reasons for consultation in general practice. CLBP is usually defined as pain, on most days of a three months period, in the back area from underneath the costal margin to the gluteal fold [1]. In some cases chronic localized pain syndromes can appear in combination with chronic widespread pain (CWP). Wolfe et al. defined CWP as pain in the left and right side of the body as well as above and below the waist plus pain in the axial skeleton [2]. A Swedish cross-sectional-study found a CWP prevalence of 28% out of all female CLBP patients in primary health care [3]. It is still unclear whether CWP is a complication of chronic local pain or an independent pain syndrome [4].

The association of CWP and several physical and psychological factors are well-documented. Studies show high prevalence of comorbidities [5] (most common are anxiety and somatization disorders). CWP patients are more often of older age, female, less educated and have decreased health related quality of life [6]. They show restricted functional ability [7] and frequently receive a disability pension [8]. In addition, there is a high social and economic burden of chronic pain, especially CWP [9]. These studies are population-based cross-sectional and cannot determine the temporal relationship between predictors and the development of CWP (generalization of pain). There are few prospective studies that explore predictors for the onset of CWP. Gupta and colleagues performed a population-based prospective study (EPIFUND-study) [10]. They identified the following disorders to be associated with CWP: psychological distress (in this case anxiety, depression, somatization disorders) [10], health related quality of life [11], physical inactivity [12], and sleep disorders [13].

Previous research, including the study of Gupta et al., primarily focused on risk factors (i.e., negative aspects advancing the development of the disease and increasing the probability of illness [14]). Our aim, on the other hand, is to identify protective factors (predictors decreasing the probability of illness [14]). Our research approach has been derived from the salutogenetic concept of Aaron Antonovsky [15]. His model of salutogenesis focuses on factors enhancing health and wellbeing, which protect (healthy) individuals from potentially damaging influences. Resources like resilience, self-efficacy and coping strategies are under consideration for being protective factors for incident chronic pain syndromes. Costa et al. found a strong relationship between pain self-efficacy, pain intensity and disability in patients with a recent onset of chronic low back pain [16]. Another study by Ong et al. illustrated that psychologically resilient individuals rebound from daily pain catastrophizing through experiences of positive emotions [17]. Finally, a study by Tan et al. studied the relationship between coping, beliefs and the adjustment to chronic pain [18].

General practitioners (GP) are often the main coordinators of CLBP and CWP patients’ management. They provide longitudinal continuity of care and play a major role with respect to appropriate care and health service utilisation [19]. Therefore, epidemiological data and knowledge about distinctive features between CLBP patients and CWP patients is needed, especially for primary care setting. GPs need to have predictors to identify CLBP patients at risk of developing CWP. Knowledge about protective factors will help to support GPs in an individualized treatment approach.

### Aim of the study

The aim of our study is to provide prevalence data on CLBP and CWP for the primary care setting. The differences between both pain localizations, with respect to pain characterisation and comorbidities, will be determined. In addition, we search for risk factors and protective factors of pain generalization in primary care CLBP patients.

## Methods/Design

### Design overview

A 12 month cohort study is performed with baseline data collection (T0) and four follow ups (after 3, 6, 9 and 12 months, T1-T4).

This project is part of the research Consortium LOGIN “Localized and Generalized Muskuloskeletal Pain: Psychobiological Mechanisms and Implications for Treatment“ funded by the German Federal Ministry of Education and Research.

### Study population

For a multi centre data collection, general practitioners in the State of Hessen, Germany are approached. Due to logistical reasons, recruitment is conducted in four waves. Participating practices (doctors and assistant personnel) are asked to recruit all eligible patients who consult for CLBP during a 5 months period, including patients consulting in home visits and emergency calls. Detailed inclusion and exclusion criteria are shown in Table 1. Trained clinical monitors visit the practices to insure validity and consecutive recruitment, during two times (at beginning and at half time of recruitment period).

**Table 1 T1:** Inclusion- and exclusion criteria

**Inclusion criteria**	All patients with chronic* low back pain** as a primary or secondary consulting reason in general practice.
	*”chronic” was defined as pain during most days in the last three months.
	**”low back pain” means pain in the back area under the costal arch, but over the bottom fold (with or without pain radiation).
**Exclusion criteria**	- patients under 18 years
	- pregnant women
	- persons with insufficient fluency of speaking German language or dementia (subjective impressed by doctor)

The number of patients, who deny participation is documented along with the reasons (in an anonymized way), and these patients are accounted for our prevalence analyzes.

### Data collection

A pen and paper questionnaire is used for data collection. After written consent is obtained, patients are asked to fill in the first questionnaire. In addition, general practitioners complete a case report form for every participant. CLBP patients, having no CWP at baseline, are included in the cohort study with a 12 months follow up. They receive mailed follow up questionnaires every three months (T1-T4), and if necessary, followed by two telephone reminders. In cases where participants are unreachable, we do ten calling attempts, during different day times before aborting the reminding process. Participants, who do not return questionnaire and do not explicitly refuse future participation, will be sent the next questionnaire as scheduled.

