### Baseline measurements

For investigating distinctive features (e.g. pain characteristics) between CLBP patients and CWP patients as well as potential risk and protective factors, the following physical and psychological parameters are collected at baseline (Table 2):

**Table 2 T2:** Overview of measurement instruments and time of assessment

			**CLBP + CWP**	**CWP**	**CLBP**			
**Function**	**Construct**	**Type**	**T0**	**T1**	**T1**	**T2**	**T3**	**T4**
			baseline	3 months	3 months	6 month	9 month	1 year
**Description of sample characteristics**	Socio demographic data	German Pain Questionnaire (module S)	+					
	Pain anamnesis	Body pain drawing model	+	+	+	+	+	+
		German Pain Questionnaire (pain anamnesis)	+					
		Multidimensional Pain Inventory (part 1, social support subscale)	+					
		Multidimensional Pain Inventory (complete)						+
		Graded Chronic Pain (von Korff Index)	+					
	Pain perception	Schmerzempfindungsskala (SES)		+	+			
	Therapy course + medication	German Pain Questionnaire (therapy and medication items)	+			+		+
	Comorbidities	Self Administered Comorbidity Questionnaire (SACQ)	+					
	Psychosomatic symptoms	Symptom Check-List-90-R (SCL-90-R, Somatisation subscale)	+					
**Risk factors**	Screening: anxiety + depression	Hospital Anxiety and Depression Scale (HADS)	+					
	Trauma Screening	Post Traumatic Diagnostic Scale (PDS-d-1) (part 1 + 2)		+				+
	Critical life events	Questionnaire for critical life events		+				+
**Protective factors**	Resilience	Brief Resilience scale (RS-11)	+					
	Coping resources for back pain	Fragebogen zu Bewältigungsressourcen bei Rückenschmerzen (FBR)	+					
	Stress Management	Brief-Cope		+				+
	Self-Efficacy	GSE (General Self-Efficacy)		+				+

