### Follow up measurements for CLBP patients (cohort group)

To identify incidental CWP (primary outcome), we collected data every three months to screen for pain generalization using the **body pain drawing** model (T0-T4).

In addition the following physical and psychological parameters are collected at follow up (Table 2):

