#### Description of sample characteristics - pain characteristics

Finally, during the fourth follow up measurement point (T4) participants are asked to complete the “**West Haven-Yale Multidimensional Pain Inventory**” [25,26]. This is done to investigate if our CLBP patients can be classified into the three clusters (dysfunctional, interpersonally distressed, adaptive copers) that have been widely shown to represent different subgroups of patients with fibromyalgia [47].

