## Discussion

This cohort study will be the largest study which prospectively analyzes predictors for transition from CLBP to CWP in primary care setting. In contrast to the typically researched risk factors, which increase the probability of pain generalization, this study also focus intensively on protective factors, which decrease the probability of pain generalization. The identified risk and protective factors might aloud GPs to identify patients at risk for development of CWP. Furthermore, the acquired knowledge about protective factors will help us to develop an individualized treatment approach for GPs.

Selection bias is often the major limitation of a cohort study. The amount of psychological constructs measured in this study can be rather demanding in terms of endurance and intellectual abilities compared to usual studies in primary care setting. For our primary care study population, which includes a high proportion of older people and persons with lower educational background, it may be a problem to deal with the questionnaires. These patients might be more likely to deny participation or abort follow up.

It might be possible, that GPs are more likely to remember study recruitment, in special cases (e.g. patients with higher disease severity or special characters) or during times with a lower workload. An incomplete recruitment brings forth the risk of selection bias and lowers external validity.

Results of the baseline analysis are expected in the course of this year (2012). Follow up data will be completed, next year (2013).

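### At T4 the last reading of the primary outcome travels with the heaviest follow-up pack, and no drawing-only fallback is described

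*Protocol article*

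**What the plan says.** All patient data come on paper: "A pen and paper questionnaire is used for data collection" (Protocol article, Data collection). For the cohort the route is postal: "They receive mailed follow up questionnaires every three months (T1-T4), and if necessary, followed by two telephone reminders". If a patient cannot be reached, "we do ten calling attempts, during different day times before aborting the reminding process". After a missed wave, "Participants, who do not return questionnaire and do not explicitly refuse future participation, will be sent the next questionnaire as scheduled". The telephone is described for reminding only. No shortened or drawing-only return is described.

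The primary outcome is incident CWP. Under Follow up measurements for CLBP patients, "we collected data every three months to screen for pain generalization using the" body pain drawing, so there are four follow-up readings.

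Table 2 ("Overview of measurement instruments and time of assessment") sets the load per wave. At T4 the cohort receives the drawing, the complete Multidimensional Pain Inventory (MPI), the therapy and medication items, the trauma screening, the critical life events list, the Brief COPE and the GSE. The text confirms the MPI: "Finally, during the fourth follow up measurement point (T4) participants are asked to complete the" full inventory, for a cluster classification.

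The Discussion calls the questionnaires demanding for older patients and those with less education: "These patients might be more likely to deny participation or abort follow up". The Background reports that CWP patients are more often older and less educated.

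**The concern.** The primary outcome needs only the drawing. At T4 the drawing sits beside six other instruments, none of which supplies a baseline predictor for the logistic regression described under Statistical analysis. A patient put off by the length of the pack may return nothing, and the drawing then goes with it.

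At T1 to T3 a missed drawing is partly recoverable, because persistent CWP can still show at a later wave. After T4 there is no later wave. Two groups of events are therefore exposed: onsets in months 9 to 12, and earlier onsets in patients who missed a previous drawing and for whom T4 is the last chance of detection.

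The protocol itself names the patients it thinks more likely to stop, and its Background ties their traits to CWP. The loss may therefore be selective. The event count has no reserve against it.

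**Working it through.** **Inputs.** From Sample size: cohort of 900, 10% developing generalized pain, 10 events per predictor. From Power calculation: odds ratio 1.65 per standard deviation, alpha 0.005. From Table 2: instruments per wave. From the instrument descriptions: Brief COPE 14 subscales of 2 items, GSE 10 items, life events 22 items. No non-return rate is given, so 10, 20 and 30% are assumed.

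**1. The plan's own figure.** 900 × 0.10 = 90 events; 90 / 10 = 9 predictors. Both reproduce. The 90 is 10% of everyone enrolled, so nothing is deducted for loss.

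**2. Load per wave for the CLBP cohort, counted from Table 2.**

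| Wave | Instruments | Content |
|---|---|---|
| T1 | 2 | drawing, SES |
| T2 | 2 | drawing, therapy/medication |
| T3 | 1 | drawing |
| T4 | 7 | drawing, complete MPI, therapy/medication, trauma, life events, Brief COPE, GSE |

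Three of the T4 additions alone come to 14 × 2 + 10 + 22 = 60 items, before the 12-scale MPI, the trauma screening and the therapy items.

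**3. Events exposed at T4.** If onsets are spread evenly over the four intervals, 90 / 4 = 22.5 events fall in months 9 to 12.

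**4. Events missed.** For T4 non-return d, unrelated to onset and with T1 to T3 all returned, missed = 22.5 × d.

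| d (assumed) | T4 drawings missing, 900 × d | Events missed | Events kept | Predictors at 10 events each |
|---|---|---|---|---|
| 10% | 90 | 2.25 | 87.75 | 8 |
| 20% | 180 | 4.5 | 85.5 | 8 |
| 30% | 270 | 6.75 | 83.25 | 8 |

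Earlier onsets in patients who had missed a previous wave come on top. The documents give no figure for them.

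**5. Power.** The normal approximation is Φ(√(N·p(1−p)) × ln 1.65 − z), two-sided at 0.005. With N = 900 and p = 0.10 it gives 0.955. With p = 83.25 / 900 (30% T4 loss, non-returners counted as non-cases) it gives 0.939. Only the change matters here. The stated 0.83 comes from a simulation whose sample size and predictor correlations are not given, so this level cannot be compared with it.

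**6. Bias.** A simulation used a predictor with true odds ratio 1.65, an independent second risk factor with odds ratio 1.5 (both in the model), 10% incidence, even onset and about 30% T4 loss. The strength of the dependence of loss on each variable was assumed. Estimated odds ratio for the predictor:

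| T4 loss depends on | Event-free non-returners dropped, T1–T3 cases kept | Non-returners without earlier onset counted as non-cases |
|---|---|---|
| second risk factor only | 1.64 | 1.625 |
| second risk factor and predictor | 1.90 | 1.58 |
| both, and onset itself | 1.90 | 1.57 |

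Observed incidence moves even in the first row: 12.6% or 9.2%, against a true 10.1%.

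**The case against.** The other side has a good deal to say.

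- Nothing in the article refuses a partly completed pack or a drawing sent back alone. The handling of partial returns and the content of reminder calls could sit in the full protocol. This stands against any claim that the drawing must come with everything else. It does not remove the point, because Data collection sets out the non-return procedure down to the number of calls, and no patient is described as being told that the drawing alone is enough.
- T3 is already a drawing-only mailing, and T1 and T2 add one instrument each. This stands and confines the point mainly to T4.
- Cohort members were given an 11-entry baseline pack (Table 2), so those least able to cope may have been filtered out before follow-up. This is plausible and would reduce the T4 loss by an unknown amount.
- The Discussion speaks tentatively, about burden in general and about initial refusal as well, and does not single out T4. This also stands: it supports a possibility of selective loss, not a forecast of it.
- Some T4 non-return would occur with the drawing alone, and the classification of non-returners may be settled in an analysis plan that is not shown. Both are true, but no later analysis choice can recreate a drawing that was never returned.

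**Conclusion.** The point holds as a cheap improvement, limited mainly to T4. The final outcome reading is mailed with by far the heaviest follow-up pack, only reminders are described for non-return, and no later wave can recover the status. On the assumptions of even onset, complete T1 to T3 returns and loss unrelated to onset, 10/20/30% T4 non-return misses about 2/5/7 of 90 events. That supports 8 predictors where the plan allows up to 9, and costs little power.

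Three stronger readings are tempting, and the documents do not support them:

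- A reader might infer that a patient who fails at T4 loses the outcome altogether. Such a patient loses one of four readings, and onsets seen at T1 to T3 stay recorded.
- A reader might take the 90/180/270 missing T4 drawings as lost events. Most of those patients would have had no onset in the last interval.
- A reader might conclude that selective loss by age or education must bias the predictor associations. Where loss depends only on other covariates in the model, the simulated odds ratio barely moved. Material distortion appeared when loss also depended on the predictor, upward or downward according to how T4 non-responders are classified.

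**What to change.** 1. Place the body pain drawing on the first page of the T4 pack.
2. At the second T4 telephone reminder, offer return of the one-page drawing alone, with a reply envelope, and state that it counts as a valid outcome assessment.
3. Make the same offer to participants who decline further questionnaires but agree to give the drawing.

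The cost is one form, postage and an ethics notification, since the calls are already planned. The downside is that a few late responders may return only the drawing and omit the other T4 instruments. For the cohort, T4 is the only reading of the Brief COPE and GSE, so those descriptions would lose some data. These instruments are not baseline predictors in the primary regression, and holding the offer back until the second reminder keeps the loss small.

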### Baseline measurements

For investigating distinctive features (e.g. pain characteristics) between CLBP patients and CWP patients as well as potential risk and protective factors, the following physical and psychological parameters are collected at baseline (Table 2):

**Table 2 T2:** Overview of measurement instruments and time of assessment

			**CLBP + CWP**	**CWP**	**CLBP**			
**Function**	**Construct**	**Type**	**T0**	**T1**	**T1**	**T2**	**T3**	**T4**
			baseline	3 months	3 months	6 month	9 month	1 year
**Description of sample characteristics**	Socio demographic data	German Pain Questionnaire (module S)	+					
	Pain anamnesis	Body pain drawing model	+	+	+	+	+	+
		German Pain Questionnaire (pain anamnesis)	+					
		Multidimensional Pain Inventory (part 1, social support subscale)	+					
		Multidimensional Pain Inventory (complete)						+
		Graded Chronic Pain (von Korff Index)	+					
	Pain perception	Schmerzempfindungsskala (SES)		+	+			
	Therapy course + medication	German Pain Questionnaire (therapy and medication items)	+			+		+
	Comorbidities	Self Administered Comorbidity Questionnaire (SACQ)	+					
	Psychosomatic symptoms	Symptom Check-List-90-R (SCL-90-R, Somatisation subscale)	+					
**Risk factors**	Screening: anxiety + depression	Hospital Anxiety and Depression Scale (HADS)	+					
	Trauma Screening	Post Traumatic Diagnostic Scale (PDS-d-1) (part 1 + 2)		+				+
	Critical life events	Questionnaire for critical life events		+				+
**Protective factors**	Resilience	Brief Resilience scale (RS-11)	+					
	Coping resources for back pain	Fragebogen zu Bewältigungsressourcen bei Rückenschmerzen (FBR)	+					
	Stress Management	Brief-Cope		+				+
	Self-Efficacy	GSE (General Self-Efficacy)		+				+

#### Description of sample characteristics - pain characteristics

For pain localisations and consequently for definition of CLBP and CWP we chose the **body pain drawing model** from Pfau et al. [20], where we modified the picture of the head and food. For definition of CWP, the ACR criteria from Wolfe et al. are used [2]. To allow for a standardized, objective analysis and classification we developed an evaluation template according to Diesner et al. [21] and Harkness [22].

We used the **“German Pain Questionnaire”** to determine the characteristics and history of the pain [23]. It is the official pain questionnaire from the **German Association for the Study of Pain**. The questions cover the following aspects: socio demographic data, subjective pain description and perception, factors of pain alleviation and exacerbation, disturbance as a result of pain, subjective pain model, screening for depression and anxiety disorders, health care utilization, as well as medical and psychological comorbidities. Nagel et al. tested the feasibility and content validity in a sample of 3000 patients [24]. Comparison with external criteria (e.g. medical and psychiatric-psychological diagnoses, physician-determined chronicity of pain) showed good content validity and excellent reliability of patients statements [24]. For this study we selected the following modules: pain duration, -characteristics and –course, socio demographic data, health care utilization and medication.

To assess the partner’s reaction in response to patient’s pain, we use the social support subscale (3 items) of the “**West Haven-Yale Multidimensional Pain Inventory**” [25,26]. It is a 12 scales questionnaire measuring the impact of pain on a patient’s life, the responses of others to the patients’ communications of pain and the extent to which patients participate in common daily activities.

The reliability test of the German version (MPI-D) from Flor et al. showed moderate to high internal consistency of the different subscales (α = 0.63-0.90) [26]. For validation, every subscale was correlated with an external instrument showing moderate to high validity [26].

To classify subjective severity of chronic pain we use the “**Graded Chronic Pain**” questionnaire (GCP) according to von Korff [27]. The self-report measure uses ratings of pain intensity and pain related disability. The author suggests a hierarchical model of pain severity where medium pain intensity is represented in the lower range of pain severity, whereas measurements of intense pain together with pain related disability are higher on the scale [28]. This is a 7 item questionnaire resulting in four hierarchical categories: Grade I, low disability - low pain intensity; Grade II, low disability - high pain intensity; Grade III, high disability - moderately limiting; Grade IV, high disability - severely limiting. Grade III and IV usually imply high pain intensity. According to Klasen et al. [28], the German version of the GCP, the factor 'Disability Score' showed a high internal consistency (α = 0.88), whereas the internal consistency of the factor 'Characteristic Pain Intensity' was moderate (α = 0.68) [28]. There is a moderate to high correlation of the German GCP and its subscales to other instruments on the patient's disability (Funktionsfragebogen Hannover: Spearman’s Rho = −0.34; Pain Disability Index: Spearman’s Rho = 0.56) [28].

